## Abstract

**Introduction::**

Tuberculosis (TB) is a global infectious disease. In low-incidence countries, paediatric TB affects mostly immigrant children and children of immigrants. We hypothesize that these children are at risk of exposure to *Mycobacterium tuberculosis* when they travel to the country of origin of their parents to visit friends and relatives (VFR). In this study, we aim to estimate the incidence rate and risk factors associated to latent tuberculosis infection (LTBI) and TB in VFR children.

**Methods and analysis::**

A prospective study will be carried out in collaboration with 21 primary health care centres (PCC) and 5 hospitals in Catalonia, Spain. The study participants are children under 15 years of age, either immigrant themselves or born to immigrant parents, who travel to countries with high incidence of TB (≥ 40 cases/100,000 inhabitants). A sample size of 492 children was calculated. Participants will be recruited before traveling, either during a visit to a travel clinic or to their PCC, where a questionnaire including sociodemographic, epidemiological and clinical data will be completed, and a tuberculin skin test (TST) will be performed and read after 48 to 72 hours; patients with a positive TST at baseline will be excluded. A visit will be scheduled eight to twelve-weeks after their return to perform a TST and a QuantiFERON-TB Gold Plus test. The incidence rate of LTBI will be estimated per individual/month and person/year per country visited, and also by age-group.

**Ethics and dissemination::**

The study protocol was approved by the Clinical Research Ethics Committee of the Hospital Universitari Mútua Terrassa (code 02/16) and the Clinical Research Ethics Committee of the Fundació Institut Universitari per a la Recerca a l’Atenció Primària de Salut Jordi Gol i Gurina (code P16/094). Articles will be published in indexed scientific journals.

**Trial registration::**

Clinical-Trials.gov: NCT04236765

## Introduction

1

It is estimated that one third of the world population is infected with *Mycobacterium tuberculosis* and that 5% to 10% of those infected will develop tuberculosis (TB) during their lifetime.^[1]^ Current global figures indicate that 10 million people develop TB every year, of which 1.1 million are children.^[2]^

It is important to underscore that children have a greater risk of developing active TB after primary infection, especially before their fifth birthday.^[3]^ Significantly, children infected with *M tuberculosis* that do not develop the disease and that do not receive preventive treatment will constitute a reservoir of TB in the future.^[4]^ Consequently, the identification and administration of preventive treatment to children with latent tuberculosis infection (LTBI) are critical to the global TB control and eradication efforts.^[5–7]^

In countries with low TB incidence, the burden of disease is notably higher in the immigrant than in the autochthonous population.^[8–10]^ Importantly, this higher incidence of tuberculosis persists beyond the first years after arrival to the host country.^[11,12]^ In fact, most new paediatric TB cases in western countries occur in immigrant children and autochthonous children born to immigrant parents.^[5,8,9]^

In Europe, TB and hepatitis C are the main imported infections among the immigrant population.^[13]^ The recent increase in international travel of immigrants to their countries of origin to visit friends and relatives (VFR)^[14–16]^ and subsequent exposure to *M tuberculosis* in countries with incidences of TB higher than in the host countries could partially explain the differences in incidence between children of immigrant families and children from the autochthonous population.^[17]^ It seems plausible to associate travel-related factors with risk of contagion, including the intensity of transmission (proportional to the local TB incidence), the relationship and contact with the local population, the duration of the stay, and individual host factors.^[18]^

However, the risk of LTBI is difficult to estimate, firstly because of the lack of a gold standard for the diagnosis, and secondly due to the long incubation period before the development of the TB disease, specially in people over 5 years of age.^[18]^

Due to the little evidence on the risk factors associated to LTBI and TB in VFR children, it is crucial to elucidate the epidemiology of TB in the immigrant population and their children to better inform public health policies aimed at reducing the number of TB cases.^[19]^

The objectives of this study are (1) to estimate the incidence rate of LTBI and TB in paediatric VFR travellers when returning from the countries of origin of their parents and (2) to identify risk factors associated with LTBI and TB.

## Methods and design

2

An interventional, single group assignment, multicentre study will be carried out from June 2017 to December 2020 in Catalonia. The incidence rate of LTBI/TB in Catalonia is 12.6 cases/100,000 inhabitants and 36.3 cases/100,000 inhabitants among the general and the immigrant population, respectively.^[20]^ BCG vaccination is not included in the national programme of immunization.

### Setting and participants

2.1

Participants of the study are children that meet the inclusion criteria, attended at any of the 5 pre-travel health clinics or at any of the 21 primary health centres (PCC) involved in the study.

#### Inclusion criteria (all criteria must be met)

2.1.1

Children less than 15 years of age, either immigrants or children born in Spain to immigrant parents.Children with at least one of the parents from a high TB incidence country. We define “high TB incidence country” as a country with a TB incidence rate 3 times higher than in Catalonia, namely 40 cases/100,000 inhabitants or greater.^[6,20]^ Countries with official reports describing an incidence less than the value proposed but with some regions with ≥40 cases /100,000 inhabitants will also be considered of high incidence (Fig. 1 and Table 1 ).Children travelling and accompanying at least one of the parents to their country of origin.The duration of the trip must last a minimum of 21 days.Informed consent must be obtained from the parents or legal guardian.

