### Sample size

2.2

The sample size was calculated using the GRANMO v7.2, 2012 program for the study of paired proportions, accepting an alpha risk of 0.05 and a beta risk of 0.2 in a two-sided test. It was estimated that 492 subjects are necessary to obtain a statistically significant difference considering an initial LTBI proportion of 0% and a final proportion of 2%. A drop-out rate of 20% is anticipated.

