#### Secondary outcomes

2.4.2

1.Sociodemographic data: sex, age, country of birth, country of birth of mother and father.2.Clinical data: weight and height (before and after travel), BCG vaccination, presence of BCG scar.3.Epidemiological data: pre-travel visit date, travel date, post-travel visit date, return date of the travel, trip duration, travel country, number of people that lived in host home, travel environment (rural / urban / mixed), smokers in host home, contact with a person suspected of having TB.

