### Statistical analysis

2.6

Qualitative variables will be described using frequency tables, and quantitative variables will be determined using median, mean and interquartile range (IQR). We will use paired proportions for comparisons. The incidence rate of LTBI and TB will be estimated per individual/month and person/year per country visited and by age group. To identify factors associated with presence of LTBI or TB, the Fisher exact test or Chi-square test and the Mann-Whitney test will be used for bivariate analyses, followed by analysis of logistic regression calculating odds ratios and 95% confidence intervals. A 5% type I error will be estimated. Data will be exported from the REDCap database to PASW Statistics 25 (SPSS Inc., Chicago, IL) for statistical analyses.

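### If siblings enrol, the named child-level tests and regression overstate the evidence on trip and host-home risk factors, because family clustering is not handled

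*Protocol article*

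**What the plan says.** Section 2.1.1 of the protocol article admits "Children travelling and accompanying at least one of the parents to their country of origin", subject to age, parental origin, trip length and consent. Neither that list nor the exclusions in 2.1.2 refers to siblings or to one child per household.

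Section 2.4.2 lists the candidate risk factors. Many describe the trip or the host home: country, duration, rural or urban setting, number of residents, smokers, and "contact with a person suspected of having TB". Others belong to the child: sex, age, country of birth, weight and height, BCG vaccination and scar.

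Section 2.6 states that "the Fisher exact test or Chi-square test and the Mann-Whitney test will be used for bivariate analyses", followed by logistic regression with odds ratios and 95% confidence intervals. Incidence is to be estimated by country and age group, with no interval method named. No family or household term appears.

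Section 2.2 sizes the study on children: "The sample size was calculated using the GRANMO v7.2, 2012 program for the study of paired proportions", and "It was estimated that 492 subjects are necessary to obtain a statistically significant difference". The limitations in the Discussion cover regional incidence, country mix and test accuracy, but not clustering within families.

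**The concern.** Infection is acquired through exposure, and the Introduction itself names local incidence, contact with local people and length of stay as plausible drivers. Children of one family on one trip have nearly the same values of all three, so their outcomes are likely to be positively correlated, and their trip and host-home covariates are identical or nearly so. When outcome and covariate are both shared within a family, a method that counts each child as a separate observation understates the variance of that covariate's effect and of the overall incidence.

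The second objective, identifying risk factors, is where this matters most. The design assumption of 2% gives about 8 events among the evaluable children. One infectious person in one host home could supply several of them, and a child-level test would count each as separate evidence for whatever that home had in common.

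**Working it through.** **1. Does the planned size already allow for clustering?** Inputs from section 2.2: "accepting an alpha risk of 0.05 and a beta risk of 0.2 in a two-sided test"; initial proportion 0% and final proportion 2%; "A drop-out rate of 20% is anticipated". With an initial proportion of zero, the discordant proportion and the difference are both 0.02.

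- n = (1.960 + 0.842)² × 0.02 / 0.02² = 7.849 × 50 = 392.4, so 393.
- 393 / (1 − 0.20) = 491.25, so 492.

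This is the stated figure exactly. It contains the drop-out allowance and no design effect. Evaluable children: 492 × 0.8 ≈ 394. Expected events: 394 × 0.02 ≈ 8.

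**2. Size of the effect.** The documents give neither the mean number of children per family (m) nor the within-family correlation (ICC). The values below are assumptions. For the overall incidence and for factors constant within a family:

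- Design effect DE = 1 + (m − 1) × ICC
- True SE / naive SE = √DE
- Shortfall of the naive SE = 1 − 1/√DE
- Effective number = 394 / DE

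| m | ICC | DE | True SE larger by | Naive SE too small by | Effective number |
|---|---|---|---|---|---|
| 1.5 | 0.1 | 1.05 | 2% | 2% | 375 |
| 1.5 | 0.2 | 1.10 | 5% | 5% | 358 |
| 2 | 0.2 | 1.20 | 10% | 9% | 328 |
| 2 | 0.3 | 1.30 | 14% | 12% | 303 |
| 2 | 0.5 | 1.50 | 22% | 18% | 263 |
| 2.5 | 0.5 | 1.75 | 32% | 24% | 225 |

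Approximate true coverage of a nominal 95% interval, 2Φ(1.96/√DE) − 1, is 93.8% at DE 1.10, 92.6% at 1.20 and 86.2% at 1.75.

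**3. An interval for incidence, if one is given.** At 2%, the exact 95% interval treating 394 children as independent is 0.88% to 3.96%. Using the effective number instead, it is 0.82% to 4.05% at DE 1.10, 0.78% to 4.17% at 1.20, and 0.68% to 4.52% at 1.50.

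**4. Can one family create a significant factor?** Take 8 events in 394 children and a host-home exposure present in 20 of them (assumed). Two-sided Fisher tests:

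- 1 of the 8 events exposed: p = 0.34.
- 3 of the 8 exposed, as when one exposed family has three infected siblings: p = 0.005.

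With 40 exposed, the two values are 0.58 and 0.038. A single transmission source can thus move a factor across the 5% level.

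**The case against.** The strongest reply is that the article never mentions siblings, that its analysis section is one paragraph, and that variance estimation is commonly left to an analysis plan or full protocol not shown here. The table of study variables is also not shown, so a family identifier may already be collected. The point about inference stands: sibling enrolment and its extent are inferred from the eligibility rule. The point about silence stands only in part. The article names its tests, and Fisher, chi-square and Mann-Whitney assume independent children in their standard form. The regression wording does not exclude clustered errors, but nothing in the text points to them.

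A reader might go on to infer that every interval in the study is too narrow. The documents do not support that. Confidence intervals are promised only for odds ratios, so the incidence part applies to whatever interval is later attached to the rate. For covariates that differ between siblings, ignoring clustering need not narrow the interval.

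A reader might also take the top of the range to mean that naive standard errors are 32% too small. That figure is how much larger the true one is; the naive one is 24% too small. It also rests on a strong assumption: at 2% incidence, an ICC of 0.5 implies that 0.02 + 0.98 × 0.5 = 51% of the siblings of an infected child are infected.

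Finally, the remedy has limits. With about 8 events, from at most 8 families, robust variance is unreliable. One child per family at m = 2 leaves about 197 children and 4 expected events. This is a fair criticism, and it limits what the fix can deliver.

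**Conclusion.** The point holds conditionally. If siblings enrol, which the criteria permit and the family-trip setting makes likely, the named methods will understate uncertainty for trip- and household-level factors and for any incidence interval computed as if children were independent. Under the assumed 1.5 to 2.5 children per family and correlation of 0.1 to 0.5, the understatement runs from negligible (design effect 1.05) to material (1.75). In the middle, at 2 per family and 0.3, 394 children carry the information of about 303.

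The reproduction of 492 shows only that no clustering allowance was made. It might be read as proof that the study is too small, but without a family size or correlation in the documents no corrected enrolment figure can be fixed. The single-family result likewise depends on the assumed exposure counts and on three siblings converting. This should be put right before analysis, but it does not invalidate the design.

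**What to change.** - Record a family/trip identifier for each child, or confirm that one is already held, and carry it in coded form into the anonymised analysis file. Without it, the correction may not be possible later.
- For incidence, compute intervals with a family-level bootstrap or family-clustered robust variance.
- For the regression, use GEE or cluster-robust standard errors by family. For trip- and household-level factors, do not rely on the unadjusted bivariate p-values.
- Report the number of families enrolled, the distribution of children per family, and how many families contribute events.
- As a sensitivity check, repeat the analysis with one randomly chosen child per family.
- Describe household-level associations as exploratory, and add family clustering to the limitations.

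The cost is one database field and a few sentences of analysis wording. Intervals become somewhat wider. With about 8 events the robust errors are rough and the one-child analysis is sparse, so the count of families with events must carry much of the interpretation.

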**Figure 1 F1:**
[figure not shown]
Countries considered in the study for having regions with an incidence of tuberculosis of 40 cases/100,000 inhabitants or greater.

**Table 1 T1:**
[figure not shown]
High and low tuberculosis incidence countries.

**Table 1 (Continued) T2:**
[figure not shown]
High and low tuberculosis incidence countries.

#### Exclusion criteria

2.1.2

Children with previous TB or LTBI.Tourist travel staying in hotels and/or resorts with scarce contact with the autochthonous population.Children with primary or secondary immunodeficiency due to treatment with corticosteroids, transplantation, treatment with anti-tumour necrosis factor, or chronic renal insufficiency.Children with congenital heart disease.Children with cystic fibrosis and other congenital pulmonary diseases.

### Sample size

2.2

The sample size was calculated using the GRANMO v7.2, 2012 program for the study of paired proportions, accepting an alpha risk of 0.05 and a beta risk of 0.2 in a two-sided test. It was estimated that 492 subjects are necessary to obtain a statistically significant difference considering an initial LTBI proportion of 0% and a final proportion of 2%. A drop-out rate of 20% is anticipated.

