The lack of gold standard for LTBI diagnosis responds to its paucibacillary nature, the quiescent state of *M tuberculosis* and the localization in the mediastinal lymph nodes.^[34]^ However, this is a universal limitation in all studies on this issue.

The low positive predictive value of the screening tests of LTBI in the general population constitutes another limitation. However, in low burden countries and among high risk groups such as immigrants and VFR travellers, tests may be useful for LTBI screening.^[35]^

Similarly, the TST and interferon-γ release assays have well described limitations, which can hinder the interpretation of results and the calculation of incidence rates, especially in the case of discordant results.^[36,37]^ Again, this is a universal limitation in all studies on this issue.

The study will implement and evaluate a new detection strategy and management of LTBI in VFR children in a country with a low incidence of TB. This strategy may prove useful to design public health policies in regions with low incidence of TB with significant numbers of VFR travellers.

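### N = 492 rests on a paired before-after test against a baseline of 0% that the exclusions fix, so its nominal 5% error is not guaranteed and N is not tied to the precision of the incidence estimate

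*Protocol article*

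**What the plan says.** Section 2.2 (Sample size) uses the "GRANMO v7.2, 2012 program for the study of paired proportions", with a two-sided alpha of 0.05 and 80% power. Its conclusion is that "492 subjects are necessary to obtain a statistically significant difference considering an initial LTBI proportion of 0% and a final proportion of 2" per cent. It then adds: "A drop-out rate of 20% is anticipated". Section 2.6 (Statistical analysis) carries the method forward: "We will use paired proportions for comparisons".

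The initial 0% follows from the entry rules. Section 2.1.2 excludes "Children with previous TB or LTBI", and the Abstract says that "patients with a positive TST at baseline will be excluded". Section 2.3 has a different rule for BCG-vaccinated children: a positive TST leads to a QFT-Plus test, and the child is removed if that is also positive.

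The first objective, at the end of the Introduction, is to estimate an incidence rate. Section 2.6 plans rates over person-time, by country visited and by age group. The Discussion concedes limits of both screening tests, including: "The low positive predictive value of the screening tests of LTBI in the general population constitutes another limitation".

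**The concern.** A paired test of proportions asks whether discordant pairs split evenly between positive-to-negative and negative-to-positive. In this study no child classified as infected enters the paired comparison, so one of the two directions is empty by design. The even split cannot serve as the reference distribution, and the 5% attached to the test describes nothing that can happen in the study.

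The test becomes a count of children called positive after travel. A false-positive conversion counts as much as a true one. A significant rise from 0% could therefore be read as evidence of infection acquired during travel when test error alone might have produced it. Meanwhile the only rationale given for N serves this test, and nothing says how precisely the incidence in objective 1 will be estimated.

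**Working it through.** **Inputs.** From section 2.2: two-sided alpha 0.05, power 80%, 0% before and 2% after, 20% drop-out, N = 492. From the exclusions: zero baseline positives. Assumed, because the protocol gives no figure: a false-conversion rate f, the chance that an uninfected child who was negative at baseline is classified as infected after travel.

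**1. Reproducing 492.** With all discordance one way, the discordant proportion equals the difference, 0.02:

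n = (1.96 + 0.8416)² × 0.02 / 0.02² = 392.4, rounded up to 393.

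393 / 0.8 = 491.25, rounded up to 492.

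The figure reproduces exactly with drop-out already included. The article does not print the formula, so this reading is an inference.

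**2. What the test does when baseline positives are zero.** Let c be the number of conversions.
- Uncorrected McNemar: (c − 0)²/(c + 0) = c. This passes 3.84 at c = 4.
- Continuity-corrected: (c − 1)²/c. At c = 5 it is 3.2, at c = 6 it is 4.17, so c = 6 is needed.
- Exact: p = 2 × 0.5^c. At c = 5 it is 0.0625, at c = 6 it is 0.031, so c = 6 is needed.

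The protocol does not say which version applies.

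**3. Rejection with no travel-acquired infection.** After 20% loss, 492 × 0.8 = 393.6, taken as 394 evaluable. With c ~ Binomial(394, f):

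| Assumed f | Uncorrected, P(c ≥ 4) | Exact, P(c ≥ 6) |
|---|---|---|
| 0 | 0% | 0% |
| 0.25% | 1.8% | 0.05% |
| 0.5% | 14% | 1.5% |
| 1% | 56% | 20% |
| 2% | 96% | 80% |

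With 393 children the figures differ by less than one percentage point. Rejection passes 5% once f exceeds about 0.35% (uncorrected) or 0.67% (exact). The last row is also the power against 2% true conversion with perfect tests: the test cannot tell 2% infection from 2% test error.

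**4. Precision that the size delivers.** For 8/393 = 2.04%, the exact (Clopper-Pearson) 95% CI is 0.88% to 3.97%.

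**5. Effect of f on the estimate.** If all true infections are detected, the observed proportion is p + (1 − p)f, so p = (0.0204 − f)/(1 − f). This gives about 1.5% at f = 0.5%, 1.0% at f = 1% and close to 0 at f = 2%.

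**The case against.** The strongest reply is that the 5% level may well hold. With perfect tests the rejection rate is 0%, and at f = 0.5% the exact test rejects only 1.5% of the time. The remark on low predictive value is limited to the general population, the Discussion adds that the tests may be useful in high-risk groups such as these travellers, and predictive value is not a false-conversion rate. Section 2.5 also requires repeat testing for grey-zone QFT-Plus values and for discordant results. All of this stands. It rules out the claim that the test cannot hold 5%, but it does not restore control: the error is still set by an unstated f and by N. The effect of the repeats on the final classification is not given either, and for discordant results only the negative test is repeated.

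Second, section 2.6 never calls the paired comparison the main analysis, and it does plan incidence rates. A reader might infer that objective 1 goes unanswered. The text does not support that; the gap is that N was not derived from those rates.

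Third, a reader might infer that the number who must complete follow-up is misstated. Section 2.2 does not say that 492 must complete, and 492 reproduces with loss included. The wording merely leaves open whether drop-out is inside the figure.

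Fourth, one could argue that children found positive at baseline erode power. If 5% or 10% of the 492 were removed, 374 or 354 would remain evaluable and exact-test power would be 76% or 71%. Those rates are assumed, the exact test is not named in the protocol, and the uncorrected test keeps 94% or 92%. The documents do not support a claim of lost power.

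**Conclusion.** The concern holds in a limited form and should be fixed. The sample-size test compares a proportion with a 0% that eligibility imposes, so its nominal 5% is not guaranteed. Depending on the version of the test, the error exceeds 5% once false conversion passes about 0.35% or 0.67%; at an assumed 1% it is 56% (uncorrected) or 20% (exact). Below those thresholds 5% is respected. These figures assume 394 evaluable children, independent results and a common f, and every non-zero f is an assumption.

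Neither the arithmetic of 492 nor the planned incidence analysis is at fault. What is missing is a link between N and the precision of that analysis.

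The absence of positive-to-negative pairs refers to LTBI as classified. The Abstract and section 2.3 treat TST-positive, BCG-vaccinated children differently, and the two must be reconciled. Under either rule, baseline LTBI as classified is 0%.

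**What to change.** - Remove the paired test against 0% from sections 2.2 and 2.6.
- Justify N by precision: about 393 evaluable children negative at baseline, expected proportion 2% (8/393), exact 95% CI about 0.9% to 4.0%. This describes the overall proportion; rates by country and age group divide the same few events and will be less precise.
- State 492 as the number of baseline-negative children to enrol, with 20% loss included (393/0.8).
- Do not read a non-zero conversion proportion as proof of travel-acquired infection. The interval alone does not remove false conversions, so report the estimate with a sensitivity range over assumed rates, as in step 5 of the working.
- If a test is kept, use a one-sample exact binomial test against a non-zero reference stated in advance. Its power would have to be checked for the reference chosen, which the protocol does not supply.

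The cost of the precision route is wording in the protocol and any analysis plan. An interval replaces the significance claim, and no children are added.
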